## Abstract

**Introduction:**

Adverse events (AEs), defined as unintended patient harm related to healthcare provided rather than an underlying medical condition, represent a significant threat to patient safety and public health. The emergency department (ED) is a high-risk patient safety setting for many reasons including presentation ‘outside of regular hours’, high patient volumes, and a chaotic work environment. Children have also been identified as particularly vulnerable to AEs. Despite the identification of the ED as a high-risk setting and the vulnerability of the paediatric population, little research has been conducted regarding paediatric patient safety in the ED. The study objective is to generate an estimate of the risk and type of AEs, as well as their preventability and severity, for children seen in Canadian paediatric EDs.

**Methods and analysis:**

This multicentre, prospective cohort study will enrol patients under 18 years of age from nine paediatric EDs across Canada. A stratified cluster random sampling scheme will be used to ensure patients recruited are representative of the overall ED population. A rigorous, standardised two-stage process will be used for AE identification. The primary outcome will be the proportion of children with AEs associated with ED care in the 3 weeks following the ED visit. Secondary outcomes will include the proportion of children with preventable AEs and the types and severity of AEs. We will aim to recruit 5632 patients over 1 year and this will allow us to detect a proportion of patients with an AE of 5% (to within an absolute margin of error of 0.6%).

**Ethics and dissemination:**

Ethics approval has been obtained from participating sites. Results will be disseminated through presentations, peer review publications, linkages with emergency research network and a webinars for key knowledge user groups.

**Trial registration number:**

This study is registered at Clinicaltrials.gov (NCT02162147; https://clinicaltrials.gov/ct2/show/NCT02162147).

Strengths and limitations of this studyThis will be the first prospective cohort study to generate an estimate of the risk and type of AEs, as well as their preventability and severity, for children seen in paediatric emergency department (EDs).This study is an essential first step to understand how to improve the safety of paediatric EDs and ultimately children's health outcomes.Many children are also seen in general or adult-oriented EDs and thus generalisability to these settings maybe limited.

## Introduction

Patient safety has been identified internationally as a healthcare priority.^1^
^2^ Adverse events (AEs), broadly defined as unintended harm to the patient that is related to healthcare and/or services provided to the patient rather than the patient's underlying medical condition,^3^ represent a significant threat to patient safety and public health.^4–7^ Canadian data suggest 7.5% of hospitalised adults suffer AEs and one-third of these events are preventable.^6^ On a national level, this represents up to 23 750 preventable deaths per year among hospitalised adults.^6^ Recent data demonstrate that Canadian children are also at high risk with 9.2% of children admitted to hospital suffering an AE and almost half of these events are preventable.^7^ The economic burden of AEs is also high. From 2009 to 2010, the cost of AEs in the Canadian acute care system was estimated at $1.1 billion.^8^

To date, patient safety research has focused primarily on admitted patients. However, most Canadians, and especially children, are more likely to visit an emergency department (ED) than to be admitted to hospital. Of the over 16 million annual patient visits to EDs in Canada, only 9.2% result in admission.^9^ The ED is considered a high-risk setting for AEs due to variable provider experience, visits ‘outside of regular hours’, high patient volume, and a chaotic work environment characterised by frequent interruptions.^10–14^ The need for ED-based patient safety research is made more pressing by increasing demands on the ED system. ED crowding and long wait times have been linked to increased patient mortality,^15–19^ treatment delays^20–22^ and ambulance diversions.^23^

Only one systematic review of the prevalence, preventability, severity and types of AEs in the ED has been published.^24^ The proportion of ED patients who suffered at least one AE related to care provided in the ED varied widely between the studies included in this review, ranging from 0.16% to 6.9% of all patients. No study in the review examined how commonly AEs occurred among children presenting to the ED. The results of this review also suggest that a large proportion (36–71%) of AEs may be preventable and this is at least comparable to that reported in hospitalised patients (35–51%).^4–6^
^25^ The review also suggested that the types of AEs that occur in the ED may be different than in hospitalised patients, and different between discharged and admitted ED patients.

Research has shown that children are particularly vulnerable to AEs.^7^
^26^
^27^ Reasons for this vulnerability include unique aspects of paediatric care such as weight-based medication dosing, children's inability to communicate complaints, and the physical and developmental characteristics of children that can affect treatment strategies, procedures and medication regimens.^27^
^28^ For children treated in the ED, these vulnerabilities are in addition to the stressors inherent to the ED. Despite this, little research has been conducted on paediatric patient safety in the ED. We have no evidence even about how common AEs are among children seen and treated in EDs in children's hospitals. Such knowledge is an essential first step to understand how to improve the safety of paediatric EDs and ultimately children's health outcomes.

## Objectives

The objective of our multicentre, prospective cohort study is to generate an estimate of the risk and type of AEs, as well as their preventability and severity, for children seen in paediatric EDs across the Canada. AEs will be defined as unintended harm to the patient that is related to healthcare and/or services provided to the patient. Healthcare and/or services will include the actions of individual hospital staff (both acts of omission and acts of commission) as well as broader systems and care processes.^6^

## Methods

### Study population

#### Study design

This is a multicentre, prospective cohort study. We will enrol an estimated 5632 eligible patients over a 1-year period from nine paediatric EDs across Canada. Enrolled patients will be followed up to 3 weeks after their visit to identify AEs.

#### Study settings

This study will take place in the EDs of 9 of the 12 tertiary care children's hospitals in Canada: Janeway Children's Hospital (St. John's, Newfoundland and Labrador, Canada), Hôpital de St Justine (Montreal, Quebec, Canada), the Hospital for Sick Children (Toronto, Ontario, Canada), Children's Hospital of Eastern Ontario (Ottawa, Ontario, Canada), Children's Hospital London Health Sciences Centre (London, Ontario, Canada), Children's Hospital (Winnipeg, Manitoba, Canada), Alberta Children's Hospital (Calgary, Alberta, Canada), Stollery Children's Hospital (Edmonton, Alberta, Canada), and BC Children's Hospital (Vancouver, British Columbia, Canada). All are members of the a cross-Canada research network known as Pediatric Emergency Research Canada (PERC) and have individual annual ED censuses of between 35 000 and 72 000 for a total of approximately 470 000 patient visits/year.

#### Inclusion criteria

Age less than 18 years.Patients from all paediatric Canadian Triage Acuity Scale categories (pedsCTAS (1) resuscitation (2) emergent (3) urgent (4) semiurgent, (5) non-urgent).

#### Exclusion criteria

Insurmountable language barrier that prevents informed consent and follow-up by telephone.Children and families that will be unavailable for telephone follow-up in the 3 weeks after their ED visit (eg, no telephone in the home, travelling out of the country, etc).

### Outcome measures

#### Primary outcome measure

The primary outcome will be the proportion of patients who experience an AE related to ED care within 3 weeks of an ED visit. We will use the Canadian Patient Safety Institute definition of an AE as an event that results in unintended harm to the patient, and is related to the healthcare and/or services provided to the patient rather than to the patient's underlying medical condition.^3^ Healthcare and services will be defined to include the actions of individual hospital staff as well the broader systems and care process.^6^
^7^ It will include harm related to acts of omission (failure to diagnose or treat) and commission (incorrect diagnosis or treatment, or poor performance).^6^ ED care will be defined as any care provided in the ED and will explicitly include care provided by ED specific staff (ie, staff physicians, nurses and allied healthcare providers) and care provided by consultants in the ED. Such a broad definition of ED care was chosen to reflect the overall patient experience and to be consistent with other studies.^12^
^13^ The time frame for primary outcome estimation (3 weeks) is based on research documenting that the majority of AEs for adult-related ED care happen within 72 h of the ED visit, that 85% occur within 2 weeks, and that the remainder occur within 3 weeks.^12^
^13^

#### Secondary outcome measures

*Proportion of patients experiencing a preventable AE:* A single physician reviewer will use a four-point Likert Scale (see online supplementary appendix 1) to determine preventability and must also identify the factor that made the event preventable.*Clinical severity of AEs:* We will report only the most severe AE for a given child. We will take a broad, inclusive, patient-oriented perspective when considering what constitutes harm to the patient. As a result, we will classify severity according to two schemes. First, for all patients, we will utilise a previous published schema developed for studies including outpatients and report the clinical severity of AEs as: (1) an abnormality on laboratory testing, (2) ≤1 day of symptoms, (3) >1 day of symptoms, (4) non-permanent disability (5) permanent disability or (6) death.^12^
^13^
^29^ Non-permanent disability will be defined as temporary impairment of function lasting less than 3 months. Permanent disability will be defined as a permanent impairment of function. Given that we will have only 3 weeks of follow-up information for most patients, the degree of disability (non-permanent or permanent) will involve the physician reviewers’ clinical judgment. For admitted patients, we will also report clinical severity according to categories used by the Institute for Healthcare Improvement (IHI) trigger tool: (1) temporary harm to the patient requiring intervention, (2) temporary harm to the patient requiring initial or prolonged hospitalisation, (3) permanent patient harm, (4) intervention required to sustain life, or (5) death.^30^*Types of AEs:* We will use a classification coding used in previous ED based studies:^12^
^13^ (1) *Diagnostic issue:* documented signs, symptoms, laboratory tests or imaging not acted on, or an indicated diagnostic test not ordered; (2) *Management issue:* suboptimal management plans despite accurate diagnosis, or based on an inaccurate diagnosis; (3) *Unsafe disposition decision:* patient placed at unnecessary risk of experiencing death or major disability by being discharged from the ED or hospital; (4) *Suboptimal follow-up:* problems with follow-up arrangements led to the development of new symptoms, unnecessary prolongation of symptoms, an unscheduled return visit to the ED, or a subsequent unscheduled hospital admission (this could be due to inadequate availability of follow-up or due to inappropriate follow-up arrangements); (5) *Medication adverse effect:* patient experiences a symptom related to a medication regardless of whether the medication was appropriately prescribed or taken; (6) *Procedural complication:* patient experiences adverse consequences of a procedure; (7) *Nosocomial infection:* infection acquired in ED or in hospital.*System response required for AEs:* The response will be classified as: (1) no treatment (symptoms only), (2) required medical/surgical intervention, (3) visit to medical doctor (MD) office, (4) visit to health laboratory/other health facility, (5) ED visit, (6) admission to hospital, (7) transfer to critical care, and (8) death. These previously published broad categories were chosen in order to address the effect of the AE at both the patient and healthcare system level.^12^
^13^
^29^ These categories are not exclusive.*Proportion of patients for whom an AE is related to ED specific care* (vs consulting specialty service care provided in the ED or care provided after the child's ED visit).*AEs related to care provided in the ED by consulting service*.*AEs that occur within the 3-week time frame but are not related to care received in the ED* (including those related to in-hospital care and primary care).*Patient and system level characteristics associated with AEs and preventable AEs*. These characteristics are further defined and described in online supplementary appendix 2.

### Sampling method

A stratified cluster-sampling scheme will be used to select shifts within each participating hospital. Patient presentations to the participating hospitals vary by time of day, time of the year and to a lesser extent day of the week. ED staffing, as well as hospital staffing levels and services, also vary by time of year, time of day and day of week. Studies have suggested that patients may have worse outcomes when presenting ‘outside of regular hours’.^31–33^ Owing to these factors, shifts within each hospital will be randomly sampled using a permuted block randomisation procedure to ensure balance by month, weekend/weekday and time (daytime 0800–1559, evening 1600–2359 h, and night 0000–0759 h).

### Overview of data collection procedures

Research assistants (RAs) collecting data in the ED, and research nurses completing telephone follow-up procedures, will use portable tablets (iPads) for real-time, web-based data collection.

#### Data collection at the index ED visit

RAs will be present in the ED for each randomised shift, and will aim to enrol consecutive patients presenting to the ED. An RA will approach families for consent using methods in keeping with site-specific ethics requirements. At all sites, for pedsCTAS level 2 (‘emergent’) patients at all sites, the RA will confirm with the clinical leader, responsible physician or bedside nurse that is appropriate for the RA to approach these families for consent/assent for the study. Patients requiring resuscitation room care (pedsCTAS level 1) will also be recruited for the study (as they may be at particular risk for AEs).^26^ For these patients, at all sites the RA will not approach the patient or their families until their medical condition is stable, the responsible ED staff has deemed it appropriate, and they have received verbal consent from families to approach. Once informed consent (from parents and capable adolescents) and assent (from the child where applicable) is obtained, the RA will collect demographic and personal healthcare data for the child, and healthcare systems level data related to their ED visit.

#### Specific data to be collected at the index ED visit

##### Patient level data

(1) age; (2) sex; (3) languages spoken by the child and family; (4) history of recent immigration (<5 years) to Canada; (5) presenting complaint documented on the ED record; (6) medical history (eg, chronic illnesses, hospitalisations, indwelling lines, etc.); (7) current medication use; (8) triage vital signs; (9) pedsCTAS score assigned to the visit; (10) discharge diagnosis.

##### Heath care system data

Given concerns that ED crowding has adverse outcomes for patients,^15–22^ we will attempt to measure crowding in several ways. For feasibility reasons, we will collect some data items at the midpoint of the hour of triage: specifically the number of patients in the ED, number waiting to be seen by a physician, number awaiting in-patient beds and average length of time between triage and registration. We will also collect data on the length of time for initial physician assessment of the patient, the area of the ED to which patient is triaged (participating EDs are divided into high and low acuity zones, most with separate space and staffing), ambulance off-load type (for patients who arrive by ambulance), type of first healthcare provider assessing the patient (eg, trainee, physician and nurse practitioner), training level of first physician assessing the patient (trainee vs staff), number of ED and consulting physicians involved in patient care, number of end of physician shift handovers for each patient, time between consult request and consultant arrival time to disposition decision, length of ED stay and discharge disposition. We will also collect information regarding the staffing of the ED during each shift (ie, number of nurses present during a study shift, number of staff physicians and number and level of medical trainees).

##### Other data tracked for each shift

We will track the number of patients presenting, and the number approached, eligible and consenting to the study. Given the chaotic nature of the ED, there will be patients during a study shift who will not be approached for the study by the RA—for these ‘missed’ patients we will gather age, sex, presenting complaint, triage level and discharge disposition (through retrospective chart review). Patients and/or parents who are approached for the study, but refuse consent, will be asked for consent to review of their medical record for the same data as ‘missed’ patients. These data will allow us to determine the generalisability of our study sample.

#### Data collection for patients discharged home following the index ED visit

A trained research nurse will contact all patients (and/or their parents) by telephone at 7, 14 and 21 days following their visit to administer a structured interview and identify patients with flagged outcomes.

#### Data collection for patients admitted to hospital at the index ED visit

A trained research nurse will contact all admitted patients (and/or their parents) by telephone (or in person if currently admitted) at 7, 14 and 21 days following their visit to administer a structured interview and identify patients with flagged outcomes. The research nurse will also screen the medical record of all admitted patients using the Canadian Pediatric Trigger Tool (CPTT) to assess for the presence of triggers during the first 3 weeks of hospital admission. If telephone follow-up reveals the patient had an ED visit or admission to another hospital, we will attempt to obtain these records for review (having obtained consent to do so at enrolment).

#### Data collection for enrolled patients ‘lost to follow-up’

For patients ‘lost to follow-up’, the research nurse will review the medical record for ED visits, outpatient visits, and admissions, and screen for triggers and flagged outcomes. The research nurse will also search, where permitted by provincial jurisdiction, the provincial coroner's database.

### Determining AEs

An established two-stage process, based on the seminal Harvard Medical Practice Study,^5^ will be used to identify AEs by first flagging outcomes and triggers to identify patients at high risk for AEs, and then reviewing their healthcare records.

#### Stage 1: identification of flagged outcomes and triggers

##### Flagged outcomes identified by telephone follow-up among discharged and admitted patients

A structured telephone interview modified from that used in other ED-based AE studies will be used to identify flagged outcomes on telephone follow-up.^12^
^13^ A child will be considered to have a flagged outcome on telephone follow-up if they experience any of the following: new symptoms, worsening symptoms, new exacerbation of a chronic underlying illness, unscheduled visit to ED or health professional, unscheduled admission to hospital or death. We will also specifically elicit and consider as flagged outcomes any family or patient report of possible: medication problem, complication of care, miscommunication between staff, miscommunication between staff and family or patient, equipment problem or other issues that may have harmed patient.

##### Triggers identified on medical record review among admitted patients

In addition to telephone follow-up to determine the presence of flagged outcomes, children admitted to hospital will also have their medical record reviewed for the presence of any of 35 CPTT triggers^34^ within 3 weeks of the index ED visit. The CPTT is the first validated, comprehensive trigger tool available to detect AEs in acute care facilities for medical or surgical care, consists of 35 screening criteria to identify records with possible harm.^34^ The CPTT triggers include (but are not limited to) unexpected death, any code or arrest, unplanned admission, unplanned surgery or return to surgery, infection of any kind, transfer to higher level of care, wrong site/wrong procedure/wrong patient and dissatisfaction with care.

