### Data analysis

#### Outcome analysis

Descriptive statistics will be used to describe enrolled patients. The primary outcome, the proportion of children with AEs related to ED care, will be reported with 95% CIs, accounting for the stratified cluster sampling design using SAS PROC SURVEYFREQ. Estimates of design effect will be examined. Secondary outcomes will be similarly estimated. To explore the association with AE and preventable AE of patient-level and system-level characteristics (together and separately) we will use univariate methods (PROC SURVEYFREQ) and multiple logistic regression (PROC SURVEYLOGISTIC). With sample size at follow-up of 5069, and an anticipated 5% rate of AEs, we expect approximately 253 AEs. Following the recommendation that approximately 10 events are required for each variable included in a multivariate model^38^ will allow us to include up to 25 predictor variables. Similar analyses will also be performed for preventable AEs. If 50% of AEs are preventable, we would expect approximately 126 preventable AEs, allowing us to include 12–13 predictor variables. Factors significant at the two-sided p<0.10 level on univariate analysis will be considered for inclusion in the multivariate model. When variables are highly correlated, the less clinically relevant ones will be omitted. Patient characteristics (see online supplementary appendix 2) to be examined include age, sex, language, immigration, triage level, time, weekday/weekend presentation, discharge disposition, pre-existing mental health condition, pre-existing health condition, use of any prescription medications and complex illness.^7^ System-level factors (see online supplementary appendix 2) measurable for each individual patient include length of time to see physician, number of ED staff physicians involved in that patient's care, number of ED physicians (trainees and staff) involved in that patient's care, location within the ED, need for a consultation, number of services consulted, level of physician initially managing the patient and delay to ambulance off-load for patients arriving by ambulance. System level factors pertaining to the environment of the ED around the time of patient arrival that may be markers of crowding include the overall ED census, number of patients waiting to be seen, number of patients awaiting in-patient beds and average time between patient triage and registration. Since these environmental factors may depend on the size of the ED, we will also consider as a variable the number of beds in the ED.

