
#### Subgroup analyses

Estimation of proportions of patients with AEs and secondary outcomes will be repeated for the following groups: (1) medical/surgical patients, (2) mental health patients, (3) admitted versus discharged patients, (4) children <1 year of age, (5) patients with complex medical conditions and (6) high acuity patients (pedsCTAS 1 and 2).

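### Admitted children are searched for adverse events by interview and chart, discharged children by interview alone, so the admitted-versus-discharged comparison is open to detection bias of unknown size

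*Protocol article*

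**What the plan says.** **Search in discharged children.** The section on children discharged home gives the interview schedule: "A trained research nurse will contact all patients (and/or their parents) by telephone at 7, 14 and 21 days following their visit". It states no routine record screen for this group.

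**Search in admitted children.** The section on children admitted at the index visit has the same three contacts, by telephone or in person if the child is still in hospital. It adds a record screen for every admitted child. The section on triggers repeats this: "children admitted to hospital will also have their medical record reviewed for the presence of any of 35 CPTT triggers".

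**Route to review.** Under Preparation of case summaries, a case summary is written for a child with a flagged outcome at interview or a trigger in the record. The three physicians in stage 2 work from that summary.

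**Use of disposition.** Subgroup analyses lists "3) admitted versus discharged patients" among the groups for which the proportions are repeated. Outcome analysis lists discharge disposition among the patient characteristics to be examined, with a univariate screen at two-sided p<0.10 before the multivariable model.

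**Primary outcome.** "The primary outcome will be the proportion of patients who experience an AE related to ED care within 3 weeks of an ED visit".

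**The concern.** The intensity of the search is tied to the variable being compared. If the trigger screen finds ED-care AEs that families do not report, those AEs count for admitted children, while their equivalents in discharged children stay unseen. Part of any excess in admitted children would then come from looking harder. The survey procedures named in Outcome analysis account for the sampling design; they do not correct unequal ascertainment.

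At stake is a secondary, exploratory result, but one that readers will use. The stated aim is to describe risk and the factors associated with it, and where AEs concentrate will inform the safety recommendations that the knowledge translation section plans. Both the unequal search and the analyses that depend on it are fixed in the protocol itself, so this is more than a detail left to the analysis plan.

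**Working it through.** **1. The plan's own figures.** Inputs from Sample size: proportion 5%, margin 0.6 points, 95% confidence, 10% loss.
- n = 1.96² × 0.05 × 0.95 / 0.006² = 5068.8, i.e. 5069.
- 5069 / 0.90 = 5632 enrolled.
- 5069 × 0.05 = 253 AEs.

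All three match the protocol ("With sample size at follow-up of 5069"). There is no arithmetic error, and the point does not rest on one.

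**2. Size of a spurious contrast.** Assumptions, none of them from the protocol: true ED-care AE risk of 5% in both groups; interview plus chart taken as the reference (sensitivity 1); interview alone finds a fraction s of what both routes find. The observed risk is 5% in admitted children and 5% × s in discharged children, so the spurious risk ratio is 1/s.

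| s | Discharged, observed | Risk ratio | Odds ratio |
|---|---|---|---|
| 0.95 | 4.75% | 1.05 | 1.06 |
| 0.90 | 4.50% | 1.11 | 1.12 |
| 0.80 | 4.00% | 1.25 | 1.26 |
| 0.70 | 3.50% | 1.43 | 1.45 |

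Odds ratio at s = 0.70: (0.05/0.95) / (0.035/0.965) = 1.45.

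**3. Chance of passing the p<0.10 screen.** The protocol gives no admitted share for its sites. As a proxy, take the 9.2% that the Introduction gives for all Canadian ED visits, with 5% to 15% as a range. At 9.2%, 5069 children split into 466 admitted and 4603 discharged. Use a normal approximation for two proportions, counting only results that show higher risk in admitted children. With no artefact that chance is 5%, half of the two-sided 10%.

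| s | Share 5% | Share 9.2% | Share 15% |
|---|---|---|---|
| 0.95 | 8% | 8% | 9% |
| 0.90 | 11% | 14% | 16% |
| 0.80 | 22% | 29% | 37% |
| 0.70 | 37% | 50% | 63% |

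This ignores clustering by shift. A design effect above 1 would lower these chances but leave the risk ratios unchanged.

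**4. What the common route does.** If interview sensitivity is the same in both groups, a contrast on interview-flagged AEs compares 5% × s with 5% × s, a risk ratio of 1. The price is fewer events: at the 9.2% share, the expected 466 × 0.05 = 23.3 AEs in admitted children fall to 22.1 (s = 0.95) or 16.3 (s = 0.70).

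**The case against.** **The gap may be small.** Extra searching distorts this contrast only through ED-care AEs that the chart screen finds and the interview misses. The interview's flag list is broad: new or worsening symptoms, any unscheduled visit, and any reported medication problem, complication or miscommunication. Inpatient triggers may mostly pick up harm from in-hospital care, which is a separate secondary outcome. Flagged discharged children also have their records used in the case summary. All of this stands and limits the size, but none of it helps a discharged child who was never flagged.

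**The asymmetry is partly unavoidable, and the analyses are modest.** The trigger tool is meant for acute care facilities and cannot be applied as such to a child without an admission. The subgroup section specifies no test between groups, and the regression is exploratory. This lowers the stakes and places the remedy in analysis and reporting.

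**A stronger reading: that the primary proportion is biased too.** A reader might infer this from the unequal search and from the handling of children lost to follow-up. The protocol does not support it as a demonstrated fault. Unequal search alone does not bias a pooled proportion; missed AEs do, and the protocol gives no figure for these. On the assumptions above, with lost children left out, the pooled 5% would shift by more than the 0.6-point margin only if s were below about 0.87. For lost children the plan states that "the research nurse will review the medical record for ED visits, outpatient visits, and admissions, and screen for triggers and flagged outcomes", and "The research nurse will also search, where permitted by provincial jurisdiction, the provincial coroner's database". It does not say how they enter the denominator, and an article may leave that rule to a fuller document. Even with none of their AEs detected, 10% of children kept in the denominator would move 5.0% to 4.5%, within the stated margin.

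**Conclusion.** The concern holds for the admitted-versus-discharged estimates and for disposition as a predictor. Stage 1 search is more intensive in admitted children, review depends on it, and following the plan as written lets search intensity pass for risk. The direction is towards a higher apparent risk in admitted children. The size is unknown: a spurious risk ratio of about 1.05 to 1.43 rests entirely on assumed relative sensitivities of 0.95 to 0.70 and equal true risk, and it would be 1 if the chart screen added no ED-care AEs.

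The concern does not extend to the primary proportion. Nor do the documents support restricting its denominator to children who completed telephone follow-up. That would remove, by design, groups the protocol deliberately captures from records: children who die in the ED, unstable admitted children, and mental health patients who cannot be approached for consent. Weighting cannot recover groups with no chance of an interview.

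**What to change.** In Outcome analysis and Subgroup analyses, state that:

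1. the admitted-versus-discharged comparison, and any model with disposition as a covariate, will use ED-care AEs reached through an interview flag, whether or not a trigger was also present;
2. AEs found only through a CPTT trigger will be reported separately for admitted children;
3. the all-source contrast will be shown alongside, with a note that the search differed by disposition;
4. the primary proportion stays on all detection sources, including children followed through records only. Children with no interview are outside the contrast in item 1.

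This needs no new data: case summaries already hold the flag or trigger details. The costs are small. Fewer AEs enter the contrast, so its interval is somewhat wider. It is also not perfectly like-for-like, because an admitted child may be interviewed while still in hospital, when an unscheduled visit or admission is not equally possible; the report should say so.
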